#### Oxidative stress analysis

2.4.3

Oxidative stress levels will be evaluated at the beginning (T_0_) and end (T_F_) of the nutritional intervention by measuring the TAC in whole blood. This will be done using the eBQC device (Bioquochem, Asturias, Spain).^2^ A 100 μL heparin-lithium anticoagulated blood sample will be applied to a test strip, which will then be used to evaluate the global antioxidant status by measuring Q1, Q2 and QT twice. Q1 represents the antioxidant capacity of compounds exhibiting the highest rate of free radical scavenging. These antioxidants are characterized by their rapid action and are the first to undergo oxidation. Notable examples of these fast-acting antioxidants include uric acid, ascorbic acid (vitamin C), GSH, vitamin E, CoQ10 and carotenoids (32, 33). Q2 refers to the antioxidant capacity of compounds that scavenge free radicals at a slower rate. These are known as slow-acting antioxidants. Some examples are polyphenols, alpha-lipoic acid, resveratrol and astaxanthin (32, 33). To quantify the overall antioxidant capacity, the device calculates QT, which results from the combination of contributions from both Q1 and Q2. The eBQC device utilizes electrochemistry to obtain the results. By applying variable voltage, the sample is oxidized to activate the antioxidants. As a result of this activation, electrons are released and then detected to determine the antioxidant capacity (33).

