## Abstract

Fibromyalgia (FM) is a complex disease that is characterized by chronic musculoskeletal pain and has great economic impact. FM prevalence is about 2% to 4% worldwide, affecting mainly middle-aged women, and its complex pathophysiology complicates diagnosis, treatment and the findings of solid biomarkers. Previous studies have suggested an association between the disease and oxidative stress, mitochondrial metabolism, intestinal microbiota and inflammation, providing sufficient data to support the multifactorial origin of FM. Hence, the objective of this randomized, prospective, low-interventional, double-blinded and placebo-controlled clinical trial is the development of a specific panel of FM biomarkers and the evaluation of their response to a six-month nutritional intervention based on the Mediterranean diet supplemented with extra virgin olive oil (EVOO). For this purpose, the experimental design implies the recruitment of a large cohort of female Spanish patients. Middle-aged women who meet the diagnostic criteria for FM according to the American College of Rheumatology (ACR) will be eligible, along with age-matched healthy women. Both groups will be randomly divided into placebo (olive oil, OO) and treatment groups (extra virgin olive oil, EVOO), and will provide samples at the beginning (T_0_), after 3 months of nutritional intervention (T_1_), at the end of the nutritional intervention in 6 months (T_2_), and 6 months after the end of nutritional intervention (T_F_), being enrolled for 1 year. Data will be collected through health questionnaires, and whole blood and stool samples will be taken and analyzed. Blood will be used for western-blotting and proteomic analysis of mitochondrial homeostasis and plasma proteome, while stool will undergo metagenomic analysis, respectively. This study represents the first low-interventional investigation with more than 200 participants focused on exploring the association of oxidative stress, mitochondrial metabolism, intestinal microbiota and related pathways with a nutritional intervention in the context of FM. As a result, the outcomes of this study will significantly contribute to the development of a comprehensive and robust panel of diagnostic biomarkers, and will shed some light on their modulation with non-pharmacological therapies such as nutrition.

**Clinical trial registration**: https://clinicaltrials.gov/study/NCT05921409, identifier: NCT05921409.

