### Study design

2.1

This is a randomized, prospective, low-interventional, double-blinded and placebo-controlled clinical trial. This study will be performed on adult women who meet ACR diagnostic criteria for FM (FM group), along with age-matched healthy volunteers (CONTROL group). The double-blinded, placebo-controlled, randomized experiment will be conducted by using extra virgin olive oil (EVOO) as treatment and olive oil (OO) as placebo, being under nutritional intervention in adherence to a Mediterranean diet supplemented with one of the olive oils for 6 months since the first sample collection. The participants will be assigned to each group randomly, using the balanced block randomization method. Briefly, once participants have been chosen for project enrollment, they will be tagged with an ordinal numeric code with three numbers by an employee from the company not related with the project nor the laboratory. This same employee will decide the codification of treatment (EVOO) and placebo (OO) groups, by assigning them an “A” or a “B” letter. Then, a second employee neither related with project or lab workflow, will randomly allocate these codes to 8-individuals blocks composed by 4 patients and 4 healthy volunteers. These blocks will be assigned to a treatment group by following the pattern ABBAABBA. In this process, this second employee will only have access to the date and time in which the participation form was completed as a unique identifier, as well as the condition of the participant: patient (FM) or healthy volunteer (CONTROL). This process will ensure that no one can link any code to its health condition, neither to participants’ data. Both processes will be reflected in patients’ database and documented in a password encrypted word file that will be also kept physically in a key-protected drawer during the entire project. The blinding method will be maintained until the data have been fully analyzed, and once this information is required to write the scientific communications that will be generated. As a result, both, patients and researchers will be fully blinded about treatment to be taken and health conditions from each participant code. Furthermore, by following the balanced block randomization method, the treatment and placebo group will comprise the same number of patients and healthy individuals. The study will span a total duration of 12 months, during which four blood and stool samples will be collected from each participant: the first before nutritional intervention (T_0_), the second after 3 months of nutritional intervention (T_1_), the third at the conclusion of the six-month nutritional intervention (T_2_) and the fourth 6 months after the end of the intervention (T_F_). This final timepoint have been included to check whether the identified biomarkers that response to nutritional intervention would change back again to the baseline, indicating a strong dependance between nutritional habits and these specific biomarkers. Figure 1 illustrates the workflow that will be followed in this study.

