### Intervention

2.3

In order to test this new tool as a patient monitoring instrument, the study will investigate the responsiveness of the new panel of markers associated with FM in the assessment and monitoring of treatment. The treatment group will undergo a nutritional intervention based on the Mediterranean diet using EVOO as a supplement, and the placebo group will receive OO. Both groups will be under nutritional control, with regular follow-up calls (twice a month) by their assigned nutritionist. Dietary adherence will be monitored by 24 h dietary recall, as well as a deeper nutritional interview. To avoid excessive withdraw, nutritionist will provided a wide repertoire of foods and cooking tips. The participants will receive a semi-customized list of three-week menus to exchange throughout the intervention (Supplementary material S2). Additionally, they will consume 50 ml of the assigned raw oil, freely distributed through the main meals during the day. This treatment regimen will be administered over a period of 6 months. Figure 2 illustrates the design of the nutritional intervention that will be followed.

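### The follow-up visit for total antioxidant capacity is contradictory: section 2.4.3 labels the end of the intervention T_F (month 12), but the design puts that end at T_2 (month 6)

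*Protocol article*

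**What the plan says.** Section 2.4.3 (Oxidative stress analysis) names two assessment times for TAC. Oxidative stress is to be "evaluated at the beginning (T_0_) and end (T_F_) of the nutritional intervention by measuring the TAC" in whole blood, on a test strip.

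Section 2.1 (Study design) defines the later visits differently: "the third at the conclusion of the six-month nutritional intervention (T_2_) and the fourth 6 months after the end of the intervention (T_F". The abstract gives the same meaning to the last visit: "6 months after the end of nutritional intervention (T_F_), being enrolled for 1 year". Section 2.3 (Intervention) confirms the duration: "This treatment regimen will be administered over a period of 6 months".

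Section 2.1 also gives T_F a purpose of its own. It is there to see whether markers that responded to the diet "would change back again to the baseline, indicating a strong dependance between nutritional habits and these specific biomarkers".

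Section 2.4.6 (Statistical analysis) compares the two oils by pre-post ANCOVA and does not name the visit that supplies the post value.

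**The concern.** One sentence identifies the TAC follow-up visit twice, once in words and once by code, and the two disagree. Laboratories and databases usually work from visit codes, so the code could well be the part that is acted on.

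If it is, TAC is read before the diet starts and again six months after it stops, with nothing in between. Two things follow:

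- The EVOO-OO contrast on TAC would be made after six months without the assigned oil. A null result would not show whether the oils differed while they were being taken.
- The return-to-baseline question could not be answered for TAC. With no on-diet value, no response can be identified, so there is nothing to return from.

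The marker has some weight in this trial. The Introduction makes the influence of nutrition on the biomarkers the secondary objective, and it rests the olive-oil rationale partly on antioxidant capacity. TAC is the only measurement described in the oxidative stress section.

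**Working it through.** The article computes no figure on this point, so there is none to reproduce. The check is a timeline built from the protocol's own definitions.

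**Inputs**

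- Diet period: month 0 to month 6 (abstract, sections 2.1 and 2.3).
- T_0: before the intervention (section 2.1).
- T_1: after 3 months of intervention (section 2.1).
- T_2: at the end of the six-month intervention (abstract, section 2.1).
- T_F: 6 months after that end (abstract, section 2.1).
- TAC visits: T_0 and T_F, the latter described as the end of the intervention (section 2.4.3).

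**Timeline.** T_F = 6 + 6 = 12 months.

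| Visit | Month | State | TAC if the label governs | TAC if the words govern |
|---|---|---|---|---|
| T_0 | 0 | baseline | yes | yes |
| T_1 | 3 | on diet | no | no |
| T_2 | 6 | end of diet | no | yes |
| T_F | 12 | 6 months off diet | yes | no |

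**Gap between the two readings.** 12 − 6 = 6 months.

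**On-diet TAC values after baseline.** Under the label, 0 of 2 on-diet visits carry one. Under the words, 1 of 2 does (T_2).

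**What each reading allows**

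- FM versus control at T_0: possible under both.
- EVOO versus OO at the end of the diet: possible only if the words govern.
- Return to baseline at T_F: possible under neither. It needs both an on-diet value and a T_F value, and each reading supplies only one of them.

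**Does another section settle it?**

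- Section 2.4.2 sets aside one blood tube for oxidative stress and mitochondrial work but names no visits.
- Section 2.4.1 says that the SF-36 is completed at every sample collection, four times in all. Section 2.4.3 names only two times for TAC, so TAC at all four visits cannot be assumed.
- Section 2.4.6 leaves the post visit of the ANCOVA unnamed.
- No section in the text shown schedules TAC at T_1 or T_2.

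**The case against.** The best reply is that this is a labelling slip. The wording of section 2.4.3 shows an intention to measure at the end of the intervention. On that reading TAC is taken at month 6, and the EVOO-OO comparison loses nothing. This objection stands to the extent that the article does not establish which visit is meant. A reader might infer that the on-treatment antioxidant effect is never measured, or that the sponsor deliberately chose a washout reading. The documents do not support either as fact: both depend on the code overriding the words beside it.

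A second reply concerns weight, and it also stands in part. The primary focus is a diagnostic panel of plasma and fecal markers, and the Discussion speaks of proteins and microorganisms. TAC is one assay, and the fault touches the secondary objective on response to nutrition. Oxidative stress is still a named theme of the study, so the point is not trivial.

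Third, a reader might put a number on the diluted treatment effect at month 12, or on the participants whose TAC data would be lost at month 6. The article gives no expected TAC effect and no persistence after the diet stops. Section 2.2.3 expects the groups to shrink over time, so recruitment numbers cannot stand for those present at month 6.

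A reader might also conclude that a missed T_2 reading could not be made up later. The article describes storage for plasma and cell pellets and none for whole blood, but a condensed article's silence does not prove that none is kept. The workflow figure is not shown and may carry a visit schedule. Even so, it would not remove the error in section 2.4.3.

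**Conclusion.** The point holds as an internal inconsistency: section 2.4.3 is wrong as written, because T_F is not the end of the intervention by the protocol's own definitions. That conclusion rests on the text alone and needs no assumption.

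The consequence is conditional. If the label governs, no on-diet TAC value exists, the oil comparison on TAC is made six months after the oil was stopped, and return to baseline cannot be judged for TAC. If T_F is a slip for T_2, the visit is mislabelled and the end-of-diet comparison is intact. The size of any loss in effect or precision cannot be stated from the article.

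**What to change.** Correct section 2.4.3 so that it agrees with the abstract and section 2.1: TAC is read at T_0 and T_2. State that T_2 supplies the post value for the EVOO-OO ANCOVA of TAC.

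If the return-to-baseline check in section 2.1 is meant to cover TAC, add a reading at T_F. Correcting the label alone does not provide that check.

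The correction is one line of text. A T_F reading in addition costs extra test strips, each taking 100 μL of blood, with the measurements made twice. No new visit or blood draw is needed, since section 2.1 already provides that "four blood and stool samples will be collected from each participant".

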#### Mitochondrial metabolism analysis

2.4.4

PBMC will be isolated by a protocol based on ammonium chloride from whole heparin-lithium anticoagulated blood. The samples will be mixed with this solution and then exposed to agitation and centrifugation at 600 RCF for 10 min at 4°C. The resulting cell pellet will be stored at −80°C. Protein extracts will be obtained from PBMC using a protein extraction buffer in white blood cells, containing sucrose 0.32 M, Tris-HCl 0.01 M, magnesium chloride 0.005 M, 1% of Triton-X and protease inhibitors. The separation of these extracts will be carried out using acrylamide gel electrophoresis (SDS-PAGE). The western-blot technique will be used to analyze the abundance of two proteins associated with mitochondrial metabolism: VDAC, a cation channel located in mitochondrial mass in directly linked to mitochondrial mass, and MAP1LC3B (Figure 3), an autophagosome-related protein used to assess autophagy. Additionally, vinculin will be used as a loading control throughout this procedure. To determine mitochondrial ratio, normalized levels of VDAC and MAP1LC3B will be indexed in a numerical algorithm designed with this purpose.

**Figure 3 fig3:**
[figure not shown]
Representation of VDAC and MAP1LC3B proteins along with their functions. Information obtained from Camara et al. (34) and Lee and Lee (35). Created with www.biorender.com.

#### Microbiota and intestinal permeability analysis

2.4.5

Participants will collect fecal samples using the DANASTOOL sample collection kit (Danagen; Barcelona, Spain). They will use a Fe-Col^®^ Faecal sample collection paper (Alpha Laboratories; Hampshire, United Kingdom) as a stool-catch platform. The participants will scoop a small portion of stool into the provided stool tube, which contains a liquid DNA/RNA stabilization solution. Following collection, all samples will be stored in accordance with established quality standards. Since the DANASTOOL sample collection kit has a DNA/RNA stabilization solution, samples were stored at room temperature until batch analysis. DNA extraction from fecal samples will be carried out using the DANAGENE MICROBIOME FECAL DNA KIT (Danagen; Barcelona, Spain). Briefly, 1 ml of homogenized sample was transferred to a tube containing beads to ease sample disruption. Then, samples were incubated at 70°C during 10 min. After incubation step, a thorough vortexing and centrifugation steps were applied. The upper phase was then transferred to a filtering column to extract DNA by centrifugation. The extracted DNA will then be used to analyze the composition of the gut microbiota. This analysis will involve amplicon metagenomics sequencing, in which amplicons of V3–V4 regions from the 16S rDNA will be sequenced using the Illumina MiSeq platform at HelixBioS (Madrid, Spain) facilities. A tagging and barcoding process suitable for Illumina technology will be conducted, according to manufacturer instruction. Each sample will undergo individual quantification, pooling, washing and titration using qPCR. The sequencing will be performed on the MiSeq platform with a fragment size ranging from 2 × 250 to 2 × 300, with the aim of generating 150,000 to 200,000 reads per sample. We will set the minimal number of reads per sample at 50,000 as quantity threshold, and Phred Score at Q30 as quality threshold. Samples with an average trimmed read length below 280 bp will be discarded. All these quality control procedures will be applied through MultiQC software (36) and sequencing results will be analyzed with USEARCH V11.1. Briefly, the reads will be cleaned using the UCHIME algorithm to eliminate “singletons” sequences (those that only had one copy in the total sequences), chimera sequences and possible artifacts. ZOTUs clustering will be carried out using the UNOISE algorithm at 99% identity (similarity). The sequences will be then aligned against the taxonomic database developed for the study of the intestinal microbiota, HUMAN GUT 16S (HelixBioS), with an alignment cut-off point of 99% (identity) using the algorithm USE-LOCAL. The results will be finally processed with phyloseq (37) and DESeq2 (38).

#### Statistical analysis

2.4.6

The statistical analysis will be performed in RStudio, using R v3.6.2 base packages. First, data distribution will be assessed by using the Kolmogorov–Smirnov test, which evaluates the null hypothesis that data correspond to normal distribution. In that case, in analyses of CONTROL vs. FM groups T_0_, parametric tests such as the unpaired student’s *t*-test and the Pearson correlation test will be used to investigate mean differences and correlation between quantitative variables, respectively. If data do not display normal distribution, the Mann–Whitney *U* test and the Spearman correlation non-parametric test will be applied for this purpose. Additionally, for comparison among groups when depicting nutritional intervention influence with treatment vs. placebo, pre-post analysis through analysis of covariance (ANCOVA) with multiple comparison correction will be used, since it has been shown to be the most powerful analysis for this experimental design (39). In all cases, the significance level (*α*) will be established at 0.05 so that null-hypothesis will be rejected when the *p*-value is <0.05. Tables will be used as preferred format to show descriptive data, such as demographic characteristics, stacked bar charts and/or pie charts will be used to represent distributions, bar charts and/or box and whiskers plots will be applied when showing differences in mean among groups and, finally, violin plots, volcano plots and additional statistical representations will be the format to show distribution and significance in the values found in each group.

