
The dietary habits of individuals play a key role in influencing the gut microbial community and its metabolic activities. Among healthy dietary choices, Mediterranean-style diets stand out, as they are associated with the prevention of various diseases, including cardiovascular and metabolic disorders, colorectal cancers and other chronic and acute processes (26). The positive effects of such diets are likely due to their high content of fibers, mono-and polyunsaturated fatty acids, antioxidants and polyphenols (26). Research has shown that adopting a Mediterranean-style diet leads to improvements in serum inflammation biomarkers and gene expression profiles (nutrigenomics) (27). Olive oil is an essential element in the Mediterranean diet and is known for its beneficial properties. Olive oil polyphenols possess a range of health benefits, including antioxidant, anti-inflammatory, antimicrobial, antiviral, anti-atherogenic, anti-thrombotic, anti-mutagenic and hypoglycemic characteristics. With regard to oxidative stress, consumption of high-phenol olive oil can help reduce cellular oxidative damage. Furthermore, it has the potential to lower the concentration of inflammatory markers and to enhance antioxidant capacity (28). Testing of this nutritional intervention as a therapeutic treatment in FM patients has shown that beneficial results are obtained in relation to oxidative DNA damage and antioxidant levels (29). These results could be explained by the close relationship between nutrient absorption and an adequate mitochondrial function.

In summary, FM is a chronic and complex condition that is highly underdiagnosed due to the lack of reliable biomarkers that might facilitate accurate diagnosis and disease monitoring. Hence, the primary focus of this study is to develop a targeted panel of specific plasma and fecal biomarkers capable of diagnosing this condition from readily obtained biological samples. Furthermore, the secondary objective is to investigate how nutrition can influence the modulation of these biomarkers. Identification of accurate biomarkers through this study is the key to advancing our understanding and management of FM, ultimately leading to improved patient outcomes.

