#### Adherence

2.2.3

To ensure adherence, each participant will be given individualized attention. The assigned nutritionists will maintain regular contact with the participants to assess their progress with the intervention, following a contact plan based on two phone calls per month. In addition, a phone line and a specific mail inbox ([contact]) will be created for queries, complaints and management of sample collection appointments. All the participants experiencing adverse event such as gastrointestinal complications, constipation, acute diarrhea or severe weight loss or gain will be immediately evaluated by nutritionists and proposed for withdrawal if those effects are somehow related to the nutritional intervention. Besides, the phone line will be uses for instant messaging communication with patients, to send them reminders about clinical appointments, solve some doubts about menus and olive oil consumption or adverse events assistance. A proactive communication plan has been designed to collect information regarding the reasons for the participants’ missed appointments, inactivity, or withdrawal. Additionally, in case of withdrawal or sample collection missing, the data collected will be used in the analysis, although upcoming datapoints will be unavoidably missed. Even though we will analyze a fully completed group of 250 participants at starting point (T_0_), the groups are expected to decrease while the project goes on, so patients with missing data will not be included in upcoming timepoints analysis.

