## Discussion

3

FM is a chronic condition that is characterized by pain and for which there is still no precise molecular diagnosis in the healthcare community. Therefore, the main objective of FIBROKIT is to develop a panel of specific biomarkers that can facilitate precise diagnosis and monitoring of the disease. This research will enhance our understanding of the role of oxidative stress, mitochondrial metabolism, intestinal microbiota and inflammation in the pathophysiology of FM. This study introduces a novel approach by designing a comprehensive panel of specific biomarkers for the disease which has not been previously documented. Furthermore, the inclusion of 250 patients represents a significantly larger sample size compared to similar studies, which will help to find relevant results with a strong statistical significance and power. The main goal and greatest challenge of FIBROKIT is the transfer from omics platforms to a group of proteins and microorganisms to be measured by an easy and reproducible wet-lab technique.

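### The primary aim is a diagnostic panel, but the analysis stated for FM versus control at baseline tests markers one at a time and gives no method for building a panel or estimating its discrimination

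*Protocol article*

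**What the plan says.** The Introduction gives the aim: "the primary focus of this study is to develop a targeted panel of specific plasma and fecal biomarkers capable of diagnosing this condition". The Discussion repeats it: "the main objective of FIBROKIT is to develop a panel of specific biomarkers that can facilitate precise diagnosis and monitoring of the disease". How nutrition modulates the markers is the secondary objective.

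Section 2.4.6 (Statistical analysis) covers two comparisons.

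- **CONTROL versus FM at T0 (primary aim).** The unpaired t-test and Pearson correlation, or Mann-Whitney and Spearman if the data are not normal, "will be used to investigate mean differences and correlation between quantitative variables, respectively".
- **Treatment versus placebo (secondary aim).** Here "pre-post analysis through analysis of covariance (ANCOVA) with multiple comparison correction will be used". This is the only place where a multiplicity correction is named.

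The decision rule, introduced by "In all cases, the significance level", is p<0.05 throughout.

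Other sections add tools. Section 2.4.2 names label-free differential proteomics software, section 2.4.4 combines two proteins (VDAC and MAP1LC3B) in a mitochondrial index, and section 2.4.5 sends the 16S results to phyloseq and DESeq2. On the baseline sample, section 2.2.3 (Adherence) says "we will analyze a fully completed group of 250 participants at starting point". Section 2.1 sets the patient-to-control ratio at 1:1 through "8-individuals blocks composed by 4 patients and 4 healthy volunteers".

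**The concern.** A diagnostic panel is a rule that takes several measurements on one woman and classifies her. Its merit is judged by discrimination: AUC, sensitivity and specificity. A p-value for a difference in means answers another question. A marker can differ clearly between group averages and still overlap too much to classify anyone, and a list of such markers does not say how to combine them.

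The article names no combining rule, no accuracy measure, and no hold-out set, cross-validation or external sample. Followed as stated, the primary comparison ends in a list of differing proteins and taxa. Without a named multiplicity correction, that list will contain chance findings in proportion to the number of candidates screened.

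What is at stake is the next step. If the chosen markers were then scored in the women who chose them, the accuracy would look good even with no signal.

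**Working it through.** **1. The article's own figure.** Section 2.2.1 uses n = Z²P(1−P)/d² with Z = 1.96, P = 7.5% and d = P/2:

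- P = 0.075: 3.8416 × 0.075 × 0.925 / 0.0375² = 189.5; × 1.10 = 208.5.
- P = 0.0755 (the unrounded mean of 8.4% and 6.7%): 188.2; × 1.10 = 207.0.

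The stated 206 reproduces to within 3%. The formula sizes a survey that estimates a prevalence. Neither the power of 0.80 nor any measure of diagnostic accuracy enters it, so the sample size section does not supply the missing link to the primary aim.

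**2. Aim against method.**

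| Needed for a diagnostic panel | Stated for CONTROL versus FM |
|---|---|
| Rule for combining markers | None; the index in 2.4.4 covers two proteins and measures mitochondrial status |
| Measure of discrimination | None; mean differences and correlations only |
| Protection against selection bias | None stated |
| Multiplicity control in the screen | Not named in 2.4.6 (named for the ANCOVA) |

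DESeq2 and differential proteomics work feature by feature, so they do not change the table.

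**3. False positives under the stated rule.** The number of candidates m is not in the document; 100 to 1,000 is an assumption. With no true signal the expected count is 0.05 × m: 5, 15, 25 and 50 for m = 100, 300, 500 and 1,000. With independent markers the chance of at least one is 1 − 0.95^m, which is already 99.4% at m = 100.

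**4. Same-sample accuracy on pure noise.** Assumptions: independent normal markers unrelated to FM, a 1:1 split, selection by t-test, and the selected markers combined in a linear discriminant; 60 replicates per setting. Mean same-sample AUC:

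| Selection | N | m = 100 | 300 | 500 | 1,000 |
|---|---|---|---|---|---|
| All p<0.05 | 250 | 0.679 | 0.797 | 0.867 | 0.952 |
| Top 10 | 250 | 0.732 | 0.771 | 0.781 | 0.799 |
| Top 5 | 250 | 0.675 | 0.705 | 0.722 | 0.737 |
| All p<0.05 | 206 | 0.703 | 0.826 | 0.890 | 0.970 |
| Top 10 | 206 | 0.748 | 0.787 | 0.805 | 0.825 |

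The true AUC is 0.50 in every cell. Applied to new data, the same panels gave 0.49 to 0.51. With selection repeated inside 10-fold cross-validation, the mean was 0.49 to 0.52.

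**5. What drives the bias** (N = 250, 200 replicates per setting).

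- With a 5% Benjamini-Hochberg false discovery rate before selection, no marker was chosen in 95% (m = 300) and 94% (m = 1,000) of null data sets. In the few where one was, same-sample AUC still averaged 0.65 to 0.66.
- With a short list fixed in advance (m = 7, assumed), 67% of null runs chose nothing and the rest averaged 0.59.

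The problem therefore comes mainly from omics-scale screening without correction, and it is mild for a short list.

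**The case against.** The strongest reply is that the article claims less than the concern implies. The Discussion describes biomarker discovery, asks whether plasma and stool are suitable places to look for a differential signature, and leaves clinical use to further research. Group comparisons do serve that question. The article also introduces its parametric tests as examples, and model-building detail may sit in a full protocol or analysis plan that is not shown.

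Part of this stands, and it rules out several stronger readings:

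- **That the panel will look accurate without signal.** The article plans no AUC or other accuracy claim on the baseline sample. The inflation arises only if someone takes that step.
- **That all 250 baseline samples are committed to marker selection.** The sentence in section 2.2.3 is about attrition. It neither describes selection nor rules out a split.
- **That the trial cannot answer its primary question.** That would require knowing that no other analysis exists.
- **That the 1:1 design overstates predictive value.** The article claims no predictive value and states no screening use, so applying its 7.5% prevalence to an assumed sensitivity and specificity would import a setting it does not describe.

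The simulated sizes also rest on assumed marker counts, independence and a linear score, and some of the inflation is a multiplicity problem rather than a missing classifier.

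The core does not fall. The statistics section is not silent on the primary comparison: it names the tests and fixes the threshold, and those tests do not fit the aim given in the Introduction and Discussion.

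**Conclusion.** The concern holds as a mismatch between aim and stated method, and it should be corrected. The article promises a diagnostic panel and states, for the comparison that would produce it, only single-marker tests and correlations at p<0.05. Those give neither a panel nor an estimate of discrimination. With no signal, they would return about 15 to 50 false positives from an assumed 300 to 1,000 candidates.

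The risk of falsely good accuracy is conditional on scoring the panel in the women who selected it. Under the assumptions in the working, at N = 250 and 300 to 1,000 candidates, that would show a mean AUC of 0.77 to 0.80 (top 10) or 0.80 to 0.95 (all p<0.05) where the truth is 0.50. These figures show the order of the bias and are not forecasts for this trial. Correlated markers would change them, and a corrected screen would rarely select a null panel at all.

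**What to change.** In section 2.4.6:

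1. State as the primary T0 analysis a pre-specified multivariable classifier of FM versus CONTROL. Penalised logistic regression is one suitable choice; others would serve.
2. Repeat marker selection and tuning inside every cross-validation fold.
3. Report out-of-fold AUC, sensitivity and specificity with 95% confidence intervals.
4. Keep the t/Mann-Whitney tests and correlations as a descriptive screen, with false discovery rate control across the CONTROL versus FM comparisons.
5. Describe the resulting panel as internally validated only.

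Predictive values are needed only if an intended-use population is stated.

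The cost is added analysis work and R packages beyond the base set that the section names. No new participants, samples or assays are needed. Reported accuracy will be lower than a same-sample figure would be. The change should be fixed before the baseline data are analysed by group.
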